### Recruitment

2.4

Recruitment started on November 1, 2022 and is scheduled for a period of 15 months. All women presenting at the study center as outpatients or are admitted or referred for inpatient care are screened for eligibility by trained members of the study team. For S and K1 cases, a specialist in obstetrics with expertise in Obstetric Medicine confirms diagnosis and obstetric findings before recruitment. For K2, a midwife performs recruitment after assessment during booking. Additionally, all inpatient admissions are screened on an everyday basis for eligibility. S and K1 also include pregnant women who are admitted to the inpatient department or transferred from other hospitals due to maternal or obstetric complications, and who have not previously presented to the study center for co-care. In selected cases where maternal complications of the pre-existing condition require immediate delivery, postpartum recruitment is possible (e.g., admission with status epilepticus and suspected placental abruption). If a woman is eligible for enrollment, she is provided a printed study information, personal explanation of the study content by a member of the study team and gives informed written consent.

### Assignment and stratification

2.5

Assignment to the groups and stratification is applied during recruitment by the enrolling investigator in a ratio of 2:2:1 (S:K1:K2). This ratio arises from the expected homogeneity of K2, a resource-efficient project planning and the already well-investigated population represented by K2 in existing literature. If uncertainties regarding assignment to the correct group arise, consensus meetings are held to resolve the issue. In Figure 1, we provide an overview of the recruitment and assignment process.

**Figure 1 fig1:**
[figure not shown]
Overview of the recruitment and assignment process for study group S and groups K1 and K2.

Additionally, we stratified the recruited women as follows:

parity (nulliparous vs. parous);singleton vs. twin pregnancy; andoutpatient vs. inpatient recruitment.

The rationale for stratification is the difference in the risk profiles of nulliparous vs. parous women and singleton vs. twin pregnancies. The same applies for women requiring inpatient care vs. outpatient consultation.

For every pregnant woman recruited in S, the subsequent pregnant woman who presents at the study center and meets the inclusion criteria for K1 and K2 is invited to participate. To ensure a complete and continuous stratification process analogous lists are compiled, which are only accessible to the members of the research team and are carefully handled in accordance with data protection regulations.

### Participant timeline

2.6

An overview of the participant timeline is visualized in Figure 2. Observation in S can start with preconception counseling or at any stage of pregnancy. Observation in K1 normally starts with the registration for birth but may also occur at an earlier stage of pregnancy due to obstetric complications. Observation in K2 starts with recruitment at booking. For all study participants, observation ends with discharge after delivery. Women recruited at preconception counseling who do not become pregnant during the recruitment period are excluded from analysis and studied separately.

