#### Additional group K2

2.3.3

Healthy pregnant women with a singleton fetus in cephalic presentation who register for birth at term after an uneventful course of pregnancy—i.e., low-risk women expecting an uncomplicated vaginal delivery—are invited for study participation as a second comparative group. No maternal pre-existing condition or obstetric complication, except for substituted hypothyroidism, must be present.

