### Outcome measures

2.7

The three-dimensional design of the ForMaT-Trial indicates three different outcome measures as follows:

The primary medical outcome is SMM. For its assessment, a list with previously defined indicators can be found in Table 1. It was adapted from the Centers for Disease Control and Prevention (CDC) (15) after a thorough literature review. Maternal secondary outcome measures consist of complications of pre-existing disease or obstetric complications, mode of delivery, type of anesthesia, length of hospital stay for delivery, and need for transfusion >4 units of packed red blood cells (PRBC). Perinatal secondary outcome measures are late miscarriage (>14 weeks of gestation), intrauterine fetal death, gestational age at birth, birthweight with percentile, APGAR-scores, arterial umbilical cord pH, severe neonatal complications including transfer to NICU, length of stay in NICU, and death.In the second part of our study, an analysis of associated costs and reimbursement for study participants is undertaken. This includes the evaluation of billing and cost coverage of the in-and outpatient health sector and further associated costs.The third trial part captures the experience of pregnancy planning, pregnancy, and childbirth, as well as health-related quality of life in women with pre-existing disorders, which is assessed by questionnaires at predetermined time points (Figure 2). The questionnaires are a combination of pre-validated instruments and specifically designed questions. As validated PRO-instruments, the German version of the EQ-5D-5L™ is incorporated in each questionnaire (38) and the German version of the BSS-R (Birth Satisfaction Scale-Revised) is included in the postpartum questionnaire (39, 40). Table 2 provides an overview of item count, domains that are interrogated, and content of all four questionnaires. Questionnaires are only filled out by women in study group S. Timepoints are as follows (Figure 2): during the initial antenatal consultation at the study center; during the appointment for birth planning; and in the postpartum period before discharge from the maternity department. If the initial visit to the study center occurs after 34 weeks of gestation only one antenatal questionnaire is filled out. Recruited women seeking preconception counseling are also asked to fill out a questionnaire after the appointment.

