### Statistical analysis

2.10

All medical parameters will be summarized using descriptive statistics. The primary medical outcome will be analyzed with a conditional logistic regression model to assess the effects of pre-existing medical conditions on the SMM rate. Odds ratios obtained from this model with corresponding 95% confidence intervals will be reported. Further secondary medical maternal and perinatal parameters will be compared between the study and additional groups. Additional analyses of medical parameters will be considered in subgroups given by different pre-existing conditions in the study group and are exploratory in nature. The main analysis will be performed on complete cases and the significance level will be set to 0.05. A sensitivity analysis will include the use of multiple imputation strategies to address possible missing observations.

For analysis of costs, a health economic evaluation to determine the costs associated with the interventions and services in the different groups will be conducted. This includes, for example, consultation time, laboratory tests, medical procedures, hospitalization, or medication. The resource use of implemented care of all the three groups will be captured, both for inpatient and outpatient setting. Thereafter, this resource use will be multiplied times unit prices to derive respective costs from a provider (in-and outpatient healthcare provider) and healthcare system perspective (statutory health insurance).

The items of the questionnaires will be summarized descriptively at each time point. Health-related quality of life will be analyzed as pre-specified in the manual of the EQ-5D-5L™ tariff and compared over time (42). The birth experience assessed by the German version of the BSS-R will be reported via the total score and the three subscales (stress during labor, personal attributes, and quality of care provision) (39).

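### Start of observation differs by group while the end is common, so delayed entry and selection distort the S-versus-K comparison of SMM, and some perinatal outcomes cannot occur in K2

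*Protocol article*

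**What the plan says.** Section 2.6 (Participant timeline) of the protocol article sets the start of observation by group:

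- S: "Observation in S can start with preconception counseling or at any stage of pregnancy".
- K1: "Observation in K1 normally starts with the registration for birth but may also occur at an earlier stage of pregnancy due to obstetric complications".
- K2: "Observation in K2 starts with recruitment at booking".

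The end is the same for everyone: "For all study participants, observation ends with discharge after delivery".

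Section 2.3.3 limits K2 to healthy women with a cephalic singleton "who register for birth at term after an uneventful course of pregnancy".

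Section 2.7 makes SMM the primary medical outcome and gives it no gestational window. It adds: "Perinatal secondary outcome measures are late miscarriage (>14 weeks of gestation), intrauterine fetal death, gestational age at birth", among others. Section 2.10 analyses SMM by conditional logistic regression and says of the rest: "Further secondary medical maternal and perinatal parameters will be compared between the study and additional groups".

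Section 2.5 stratifies on parity, singleton or twin pregnancy, and outpatient or inpatient recruitment. Gestation at entry is not a factor. The limitations in the Discussion name the single center and the short observation after birth, but not the unequal start.

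**The concern.** A binary outcome counted over the observed period depends on how long a woman is observed and on what had to be true for her to enter. Here both depend on group. An SMM event before birth registration, such as an embolism or acute heart failure, counts for an S woman already under observation. It cannot count for a K2 woman, because she would no longer be eligible, and it mostly cannot count for a K1 woman, who is normally not yet enrolled.

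The primary odds ratio is meant to show the effect of pre-existing conditions on SMM. As planned, it mixes that effect with differences in entry. For some perinatal outcomes the problem is structural: part of the contrast with K2 follows from the eligibility rule and says nothing about pre-existing disease.

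**Working it through.** **Step 1: the three windows side by side.**

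| Group | Start | Entry depends on | End |
|---|---|---|---|
| S | Preconception or any stage; also inpatient admission, transfer or, in selected cases, postpartum (2.4, 2.6) | Pre-existing condition; for some, a current complication | Discharge after birth |
| K1 | Normally birth registration; earlier only because of a complication (2.6) | Obstetric risk; for early entrants, a complication | Discharge after birth |
| K2 | Booking (2.6) | Uneventful course so far, cephalic singleton (2.3.3) | Discharge after birth |

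A comparison woman is the next eligible woman to present (2.5). A matched set can therefore combine an S woman in early pregnancy with a K2 woman registering for birth. The outpatient/inpatient stratum aligns entry only in part.

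**Step 2: the plan's own effect size.** Section 2.8 assumes SMM rates of 50/1000 in S and 23/1000 in K1 + K2. The odds ratio is (0.050/0.950) / (0.023/0.977) = 2.24.

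**Step 3: what delayed entry alone could produce.** Let true risk be 23/1000 in all groups, let S be observed throughout, and let a share q of SMM arise before K entry. The article gives no timing of SMM, so q is an assumption. The 2:2:1 ratio in section 2.5 makes K2 one third of K.

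- All K truncated: K rate = 0.023 × (1 − q).
- Only K2 truncated: K rate = 0.023 × (1 − q/3).
- Odds ratio = (0.023/0.977) / [K rate/(1 − K rate)].

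| q | K rate, all K truncated | OR | K rate, only K2 truncated | OR |
|---|---|---|---|---|
| 10% | 0.0207 | 1.11 | 0.0222 | 1.04 |
| 40% | 0.0138 | 1.68 | 0.0199 | 1.16 |

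This captures one mechanism only. It leaves out K1 women who enter because of a complication, which raises the K rate and lowers the odds ratio. It also leaves out S women who enter late, which shrinks the effect, and S women recruited because of a complication, which raises the S rate.

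**Step 4: what a shared window costs.** Let a share f of the planned 5.0% in S fall before the shared window, and let the K rate stay at 2.3%. Both are assumptions. Power comes from the conditional-logistic score test for 257 sets of two S and three K women, two-sided 5%. Per set, U = a − 2m/5 and V = [m(5 − m)/4] × (2/5) × (3/5), where a is the number of S events and m all events in the set. Power = Φ{[√257 × E(U) − 1.96 × √E(V)] / √Var(U)}.

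| f | S rate in window | OR | Power |
|---|---|---|---|
| 0% | 5.0% | 2.24 | 73% |
| 10% | 4.5% | 2.00 | 59% |
| 20% | 4.0% | 1.77 | 42% |
| 30% | 3.5% | 1.54 | 26% |

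The first row is 73%, not the 90% stated in section 2.8. This calculation needs about 415 sets for 90%. That is a separate matter and may reflect options of the cited method that the article does not state. Here only the fall from row to row matters.

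**The case against.** Several stronger readings are tempting, and the article does not support them.

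- **S is always observed from early pregnancy.** Section 2.6 says only that it can be. Section 2.7 provides for first visits after 34 weeks, and section 2.4 for admissions, transfers and postpartum recruitment.
- **The odds ratio is biased upwards.** Complication-triggered entry into K1 pushes it down, so the net sign is unknown.
- **This is immortal-time bias.** No group is credited with event-free follow-up that it could not have failed. Time before entry is simply not observed. Delayed entry and selection at entry are the right terms.
- **Late miscarriage is inflated by a fixed factor.** With K2 at zero and equal risk in S and K1, the ratio against pooled K would be 1/(2/3) = 1.5. But pooling is stated only for the sample size, and K1 is itself mostly observed late.
- **Early preterm birth is impossible in K2.** That depends on the booking week, which is not given. The phrase about registering at term can also mean registering for a term birth.

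The other side can add that several indicators in Table 1, such as anesthesia complications, amniotic fluid embolism and hysterectomy, belong largely to delivery; that the study aims to describe care; that K2 is low-risk by design; and that details for each outcome may sit in a separate analysis plan.

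These points limit the size of the problem and rule out a claimed direction. They do not remove it: the article itself fixes group-dependent entry, plans an effect estimate for SMM, and plans between-group comparison of perinatal parameters.

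**Conclusion.** The point holds in this form. Entry is tied to group, the end is common, and nothing in the stated design or analysis aligns the windows. The S-versus-K odds ratio for SMM is distorted by delayed entry and selection at entry. Its size and net direction cannot be computed from the article. The ranges of 1.04-1.16 and 1.11-1.68 are illustrations that rest on equal true risk, full observation of S, q of 10-40%, and truncation of K2 only or of all K. The upper figure needs every K1 woman to enter late, which section 2.6 does not say. Both ranges lie below the planned 2.24.

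For the perinatal outcomes the conclusion needs no assumed rate. Late miscarriage, and fetal death before the K2 booking gestation, cannot occur in K2 by eligibility, and gestational age at birth is truncated there. That K2 booking is late is inferred from the uneventful-course and cephalic-presentation criteria, since section 2.6 says only booking.

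**What to change.** Amend sections 2.7 and 2.10 as follows:

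1. Do not compare late miscarriage, fetal death before the K2 booking gestation, or gestational age at birth with K2 or with pooled K. Report them descriptively. Any S-versus-K1 comparison should account for gestation at enrolment and state that early K1 entry is triggered by complications.
2. Keep the planned SMM endpoint. Add a prespecified between-group SMM analysis on the window that all groups share, from birth admission to discharge.
3. Report SMM before that window separately by group.
4. List the unequal start of observation as a limitation in the Discussion.

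Replacing the primary endpoint with one restricted to women still pregnant at the K2 booking gestation is not advised. It would drop earlier deliveries in S and K1 and the antenatal SMM that the study wants to capture.

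The cost is wording and one further analysis of data already collected. The downside is fewer S events and lower power in the shared-window analysis: in the illustration above, from 73% to 42% if 20% of S events fall before the window. It should be read by its confidence interval next to the planned result.

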**Figure 2 fig2:**
[figure not shown]
Participant timeline for all three groups from initial consultation (during pregnancy or preconception) to discharge after inpatient stay for childbirth. Timepoints for questionnaire assessment in the study group are marked with letter icons.

### Outcome measures

2.7

The three-dimensional design of the ForMaT-Trial indicates three different outcome measures as follows:

The primary medical outcome is SMM. For its assessment, a list with previously defined indicators can be found in Table 1. It was adapted from the Centers for Disease Control and Prevention (CDC) (15) after a thorough literature review. Maternal secondary outcome measures consist of complications of pre-existing disease or obstetric complications, mode of delivery, type of anesthesia, length of hospital stay for delivery, and need for transfusion >4 units of packed red blood cells (PRBC). Perinatal secondary outcome measures are late miscarriage (>14 weeks of gestation), intrauterine fetal death, gestational age at birth, birthweight with percentile, APGAR-scores, arterial umbilical cord pH, severe neonatal complications including transfer to NICU, length of stay in NICU, and death.In the second part of our study, an analysis of associated costs and reimbursement for study participants is undertaken. This includes the evaluation of billing and cost coverage of the in-and outpatient health sector and further associated costs.The third trial part captures the experience of pregnancy planning, pregnancy, and childbirth, as well as health-related quality of life in women with pre-existing disorders, which is assessed by questionnaires at predetermined time points (Figure 2). The questionnaires are a combination of pre-validated instruments and specifically designed questions. As validated PRO-instruments, the German version of the EQ-5D-5L™ is incorporated in each questionnaire (38) and the German version of the BSS-R (Birth Satisfaction Scale-Revised) is included in the postpartum questionnaire (39, 40). Table 2 provides an overview of item count, domains that are interrogated, and content of all four questionnaires. Questionnaires are only filled out by women in study group S. Timepoints are as follows (Figure 2): during the initial antenatal consultation at the study center; during the appointment for birth planning; and in the postpartum period before discharge from the maternity department. If the initial visit to the study center occurs after 34 weeks of gestation only one antenatal questionnaire is filled out. Recruited women seeking preconception counseling are also asked to fill out a questionnaire after the appointment.

**Table 1 tab1:** Indicators of SMM, adapted from the definition of the Centers for Disease Control and Prevention (CDC) (15).

Indicators for severe maternal morbidity (SMM)	ICD-10 short/OPS-Codes
Acute renal failure	N17.-, O90.4
Cardiac arrest/ventricular fibrillation	I46.-; I49.0-
Heart failure/arrest during surgery or procedure	I97.12-; I97.13-; I97.710; I97.711
Shock	O75.1; R57.-; R65.2!; T78.2; T88.2; T88.6; T81.1
Sepsis	O85; T80.2; T81.4, R65.-!, A40.-; A41.-; A32.7
Disseminated intravascular coagulation	D65; D68.8; D68.9; O72.3
Amniotic fluid embolism	O88.1-
Air and thrombotic embolism	I26.-; O88.0-; O88.2-; O88.3-; O88.8-
Puerperal cerebrovascular disorders	I60-I69; O87.1; O87.3
Severe anesthesia complications	O74.- O89.-
Pulmonary edema/acute heart failure	J81.; I50.-
Adult respiratory distress syndrome	J80.-
Acute myocardial infarction	I21.-, I22.-
Eclampsia	O15.-
Sickle cell disease with crisis	D57.0-
Aneurysm	I71.-; 72.-
Ventilation	OPS 8–713
Temporary tracheostomy	OPS 5–311
Conversion of cardiac rhythm	OPS 8–64
Transfusion of blood products (≥4 PRBC or ≥ 2 red PRBC + ≥2 fresh frozen plasma)	OPS 8–80,8–81
Hysterectomy	OPS 5–75
Maternal death	O97.-

**Table 2 tab2:** Item count and domains of the four questionnaires at the pre-defined time points (see Figure 2).

	Questionnaire 1	Questionnaire 2	Questionnaire 3	Questionnaire 4
Time points	Preconception counseling	Initial consultation	Birth planning	Postpartum period
Number of items	38	53	56	48
Domains	Inner conflicts Barriers Motivation Social support system Sources and quality of information	In addition to domains of Questionnaire 1: Perception of pregnancy Course of pre-existing condition	In addition to domains of Questionnaire 1: Perception of pregnancy Course of pre-existing condition Issues of childbirth	In addition to domains of Questionnaire 1: Breastfeeding Preparedness for postpartum period
EQ-5D-5L™, 6 items	✓	✓	✓	✓
BSS-R, 10 items				✓

Domains specifically refer to the pre-existing conditions.

Further items were established in a multistep process. An initial collection of main topics was developed via literature research, discussed in a consensus meeting with the team of the Center for Rare Diseases of the University Hospital Bonn, and transferred into a catalog of questions by the interprofessional study team. As an important next PRO-measure step, the catalog of questions was sent to 15 national umbrella organizations of patient advocacy groups, such as adults with congenital heart disease, inflammatory bowel disease, or familial adenomatous polyposis. The feedback and comments of affected persons were included in the catalog and an expert in statistics ultimately proofread the questionnaires. Thereafter, a pre-test was performed by at least two affected women, midwifes, medical students, and physicians.

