#### Study group S

2.3.1

Women with pre-existing medical conditions, presenting either pregnant or for preconception counseling, are invited to join the study. For our study, we defined pre-existing condition as the presence of chronic diseases (e.g., multiple sclerosis) or of sequelae of a preceding health incident (e.g., history of pulmonary embolism). A list of included conditions can be found in Supplementary Table 1. It is important to emphasize the fact that only severe conditions, which may have an impact on the course of pregnancy and/or delivery and/or on women’s perception of pregnancy are included. Therefore, pre-existing conditions which appear to be irrelevant for pregnancy outcome and women’s perception are explicitly excluded. For the latter, in Supplementary Table 2, we provide a list of conditions considered to be irrelevant for our investigation, meaning that women exclusively fulfilling these diagnoses are not included in the study (e.g., essential hypertension without medication before pregnancy). Both selection processes were undertaken by consensus meetings of the research team. Uncertainties regarding inclusion or exclusion of rare or exceptional cases are resolved in a consensus meeting with two Obstetric Medicine experts on a case-by-case decision (e.g., sarcoidosis without functional impairment).

Women in study group S are required to understand and complete the questionnaires in German language. If a woman is willing to participate in the study but not capable to complete the questionnaires due to language barriers, recruitment is possible for analysis of medical outcome and economic evaluation only.

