### Data collection and management

2.9

Trial data consist of three categories: medical outcome data, economic data, and questionnaires. Medical outcome is collected via database query of the hospital information system ORBIS (Dedalus Healthcare, Bonn, Germany), the ultrasound software ViewPoint™ (Version 6, GE HealthCare, Solingen, Germany), and the pediatric software Neodat (Version 5, Paedsoft, Tuebingen, Germany). Economic data are collected via database query of the information system SAP (SAP R/3 ECC 6.0, IS-H Release 617 Package, Walldorf, Germany). All questionnaires are completed online with the assistance of a study team member. Data management and monitoring is performed by the Clinical Support Study Center of the University Hospital Bonn, Bonn, Germany. All relevant trial data are entered in a specifically build REDCap© database (Version 12.0.27, Nashville, Tennessee, United States).

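### Table 1 counts whole code families as severe maternal morbidity with no new-or-acute rule, so a long-standing diagnosis could count as a primary event in group S only

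*Protocol article*

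**What the plan says.** Section 2.7 fixes the primary outcome: "The primary medical outcome is SMM. For its assessment, a list with previously defined indicators can be found in Table 1". Table 1 pairs each indicator with ICD-10 or procedure codes. Three rows matter here:

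- Puerperal cerebrovascular disorders: "I60-I69; O87.1; O87.3".
- "Pulmonary edema/acute heart failure": J81 and all of I50.-.
- Aneurysm: I71.- and 72.- (presumably I72.-), with no qualifier in the label or the codes.

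On ascertainment, section 2.9 says: "Medical outcome is collected via database query of the hospital information system ORBIS", together with an ultrasound and a paediatric system. It mentions data management and monitoring, but no check of whether a diagnosis is new.

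The groups are defined by the presence or absence of chronic illness. For S (section 2.3.1): "we defined pre-existing condition as the presence of chronic diseases (e.g., multiple sclerosis) or of sequelae of a preceding health incident". For K2 (section 2.3.3): "No maternal pre-existing condition or obstetric complication, except for substituted hypothyroidism, must be present". Section 2.3.2 sets the same bar on pre-existing conditions for K1, with an exception for uncomplicated, substituted hypothyroidism.

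Two transfusion thresholds also appear. The secondary outcome in section 2.7 is "need for transfusion >4 units of packed red blood cells (PRBC"), while the Table 1 row reads "Transfusion of blood products (≥4 PRBC or ≥ 2 red PRBC + ≥2 fresh frozen plasma").

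**The concern.** The primary analysis (section 2.10) is a conditional logistic regression of SMM on having a pre-existing condition. It is meant to show whether such women suffer more severe complications. If a code that records the pre-existing condition itself also satisfies the outcome list, some events in S would reflect how the group was selected. The comparators cannot contribute events by that route. The error would be one-sided: it raises the SMM rate in S and leaves K1 and K2 untouched. With a rare outcome, a handful of such women is enough to move the odds ratio.

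**Working it through.** **Step 1: does the printed list separate new events from old diagnoses?** Some rows do so through the codes. Sickle cell disease counts only with crisis (D57.0-), and renal failure only as N17.- and O90.4. The three rows above do not. Two have labels that point to puerperal or acute events, but the codes beside them are entire families. The third has no limit at all. That these families include non-acute and sequela codes is a property of the ICD-10 classification, which the article uses but does not reproduce.

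**Step 2: who can carry such a code in?** Only S. Section 2.3.1 admits chronic disease and sequelae, and the Discussion says conditions from all medical specialties are included. Sections 2.3.2 and 2.3.3 bar them from K1 and K2. Acute events under the same codes remain possible in every group.

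**Step 3: the planned effect.** Section 2.8 assumes SMM of 50 per 1,000 in S and 23 per 1,000 in K1 + K2.

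- Implied odds ratio: (0.050/0.950) / (0.023/0.977) = 0.05263 / 0.02354 = 2.24.
- Planned analysis set: 257 sets of 2:3, so 514 S and 771 K women.
- Planned gap: 0.027 × 514 = about 14 S women.

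The 257 sets themselves were not reproduced. A score test with independent outcomes within sets needs 415 sets for two-sided 90% power. The cited method may use inputs the article does not give. That is a separate matter, and the odds ratios below do not depend on it.

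**Step 4: no true effect, some carried-in codes.** Let q be the share of S women who meet Table 1 only through a carried-in code. The documents give no value, so q is an assumption. With a true rate of 0.023 in both groups:

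Apparent S rate = 0.023 + q × (1 − 0.023)

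| q (assumed) | S women of 514 | Apparent S rate | Odds ratio vs 0.023 | Chance of a significant excess in S |
|---|---|---|---|---|
| 0.5% | 2.6 | 0.0279 | 1.22 | 8% |
| 1% | 5.1 | 0.0328 | 1.44 | 19% |
| 2% | 10.3 | 0.0425 | 1.89 | 51% |

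For q = 1%: 0.0328/0.9672 = 0.0339, and 0.0339/0.02354 = 1.44. The last column uses the same score test with 257 sets, two-sided 5%. With no carried-in codes it would be 2.5%.

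**Step 5: the other direction.** If the planned 0.050 already includes carried-in codes, the rate of new events in S is 1 − 0.950/(1 − q). At q = 1% this is 0.040, odds ratio 1.79. At q = 2% it is 0.031, odds ratio 1.34.

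**Step 6: transfusion.** A woman given exactly 4 units of packed red cells is a primary event by Table 1 but not a secondary event by section 2.7. This affects all groups alike and is unrelated to Steps 1 to 5.

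**The case against.** The strongest reply is that the article already says what SMM means. Section 1.1 describes it as complications arising in pregnancy, childbirth and the postpartum period, and sections 2.1 and 2.6 fix the observation window. A stable aneurysm or an old stroke does not fit, and two of the three row labels agree. Code handling and adjudication may also be set out in the full protocol or analysis plan. This stands as evidence of intent. It does not settle the matter, because the article prints the operational list. A chronic diagnosis can be coded again at any visit or admission inside the window, and the codes do not enforce the intent. The aneurysm row does not even express it.

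A second reply is that the list derives from the CDC and was kept for comparability (Discussion). That is a real benefit. But a standard list does not remove the problem when one group is selected for chronic disease and the others for its absence.

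Several stronger readings are tempting and are not supported:

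- A reader might infer that affected S women are SMM-positive from entry, or that part of the effect is certainly built in. Both need the relevant diagnoses to be eligible (Supplementary Table 1 is not shown) and codes to be matched without a clinical check.
- A reader might infer that K women cannot have these codes. They are barred only from bringing them in as prior conditions.
- A reader might infer that the whole planned effect could be artefact, since q = 2.7% gives an odds ratio of 2.21. That q is simply the planned gap of 27 per 1,000 put back in, so the match is circular.
- A reader might infer that the claimed advantage over billing-data studies fails. Section 2.9 takes medical outcomes from clinical systems and economic data from a separate one, so this is not shown.

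**Conclusion.** The point holds as a fault in the printed definition of the primary outcome. Three rows use code families wider than an acute event, no code-level onset rule is stated, and a carried-in diagnosis can arise only in S. Any resulting bias raises the odds ratio. Its size cannot be determined from the article. The values 1.44 and 1.89 illustrate assumed shares of 1% and 2%, with equal true rates of 23 per 1,000 and outcomes treated as independent within sets. They show that about 5 to 10 women among 514 would matter; they do not estimate how many there will be. Eligibility of each diagnosis is inferred from the general definition of S. The change should be made before the outcome query is run. The transfusion mismatch is a minor wording point.

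**What to change.** 1. In Table 1, restrict the I60-I69, I50.- and I71.-/72.- rows to acute sub-codes. Alternatively, count them only when the event, or an acute decompensation of a known condition, arose in the index pregnancy up to discharge.
2. Tie the rule to onset in the index pregnancy, not to enrolment. Section 2.4 enrols women admitted or transferred with complications and allows postpartum recruitment in S, so an after-enrolment rule would delete genuine events.
3. Confirm code-positive cases in all groups from the chart against written criteria, by reviewers who are not told the group. Charts may reveal it, so the reviewers should not be those who assigned the groups. At the planned rates this is 514 × 0.050 + 771 × 0.023 = about 43 women in the analysis set, or 600 × 0.050 + 900 × 0.023 = about 51 of all 1,500.
4. Add a sensitivity analysis that excludes indicators matching the woman's qualifying condition. Keep it out of the primary analysis, because it can also remove true acute decompensation.
5. Reconcile the transfusion threshold between section 2.7 and Table 1, or state that two different thresholds are intended.

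The cost is an edit to Table 1 and section 2.7, a data rule and a short chart check. The qualifying diagnosis is already confirmed at recruitment. The downsides are fewer S events, hence less power, and slightly less comparability with studies using the CDC list. Reporting the unrestricted list alongside would keep that comparison.
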